## Abstract

**Background:**

Seniors with recurrent hospitalizations who are taking multiple medications including high-risk medications are at particular risk for serious adverse medication events. We will assess whether an expert Clinical Pharmacology and Toxicology (CPT) medication management intervention during hospitalization with follow-up post-discharge and communication with circle of care is feasible and can decrease drug therapy problems amongst this group.

**Methods:**

The design is a pragmatic pilot randomized trial with 1:1 patient-level concealed randomization with blinded outcome assessment and data analysis. Participants will be adults 65 years and older admitted to internal medicine services for more than 2 days, who have had at least one other hospitalization in the prior year, taking five or more chronic medications including at least one high-risk medication. The CPT intervention identifies medication targets; completes consult, including priorities for improving prescribing negotiated with the patient; starts the care plan; ensures a detailed discharge medication reconciliation and circle-of-care communication; and sees the patient at least twice after hospital discharge via virtual visits to consolidate the care plan in the community. Control group receives usual care. Primary outcomes are feasibility — recruitment, retention, costs, and clinical — number of drug therapy problems improved, with secondary outcomes examining coordination of transitions in care, quality of life, and healthcare utilization and costs. Follow-up is to 3-month posthospital discharge.

**Discussion:**

If results support feasibility of ramp-up and promising clinical outcomes, a follow-up definitive trial will be organized using a developing national platform and medication appropriateness network. Since the intervention allows a very scarce medical specialty expertise to be offered via virtual care, there is potential to improve the safety, outcomes, and cost of care widely.

**Trial registration number:**

ClinicalTrials.gov identifier: NCT04077281.

**Supplementary Information:**

The online version contains supplementary material available at 10.1186/s40814-024-01484-6.

## Background

Current systematic reviews of randomized trials to manage polypharmacy or to manage medications in hospital or in the transitions of care have not consistently shown improvements in important clinical outcomes [1–5]. This is largely because (a) the interventions have been carried out by providers without the requisite combination of diagnostic, therapeutic, and risk management expertise or authority to make requisite changes, (b) the intervention was not sufficiently concentrated (too short, incomplete, or misdirected), (c) the medication focus was misplaced (i.e., not high-risk medications, which are the most associated with adverse clinical outcomes), (d) the outcomes were overly focused on poor quality surrogates for clinical outcomes, or (e) the patient has so much irreversible comorbidity that changes in medications could not have significant impact.

Because of the huge potential burden of harm and the number of affected vulnerable older adults in most countries, the value of more randomized trial inquiry is high. There is enough suggestion of benefit from trials on prescribing appropriateness combined with the potential for major medication safety improvements, to support an expert intervention concentrated on the highest risk group as they transition through a very high-risk period targeting the highest risk medications [4, 6–9]. In addition, recent advances in digital health make it reasonable to focus on utilizing clinical pharmacologist expertise for this high priority problem within robust communication systems that support patient consultation and follow-up from any geography no matter how remote. Clinical pharmacologists are medical specialists, in this case with internal medicine cross-specialization, who regularly lead the care of hospitalized medically complex patients and formulate their therapeutic priorities.

Transitions in care, particularly in- and out-of-hospital and high alert medications, are two primary high-risk medication safety situations referenced by WHO in their Global Patient Safety Challenge [10]. Even with evidence of under-detection, systematic reviews of the literature conclude that adverse drug events (ADEs) amongst older adults lead to approximately 1 in 10 hospitalizations [11–13]. Adverse drug-related hospital admissions appear to be directly correlated with the number of medications taken concurrently, the number of prescribers involved, possibly the number of pharmacies used, and with hospitalization within the previous year [14]. In several studies, female sex was also a risk factor. Once in hospital, patients (*n* = 46,626) remained at high risk of ADEs, with a mean prevalence of 21.6% (*SD* 16.7), 20.7% of these judged to be severe or life threatening and 32.3% (*SD*22.6%) judged to be preventable [15]. In addition to the risk factors above, a complex patient (several comorbidities with several provider experts involved) is significantly more likely to suffer adverse events in hospital [16, 17]. The period immediately following hospital discharge remains high risk with 37% of seniors sustaining medication-related harm (81% serious) within 8 weeks [18]. In this cohort study from the UK, female sex was associated with medication-related harm [18]. The outcomes of ADEs included prolonged length of stay, frequent readmission, emotional trauma, high costs, and death [16, 19, 20].

The prevalence of major polypharmacy defined as the concurrent, regular use of 10 or more medications is high amongst seniors reaching 38.4% in those aged 85 years and older [4, 21]. While the number of medications dispensed remains a useful signal, it is impossible to gauge the quality of medication regimens simply by the number of medications, as this does not account for the patient’s main diagnosis, comorbidities, risk factors, past history of medication use, or the benefit-harm ratio of the drug for that patient. For example, an older patient with diabetes frequently requires two glucose lowering medications, a statin for cholesterol, and two to three medications for blood pressure, just to manage their high cardiovascular risk without treating their other health problems. Thus, the medication safety target is problematic polypharmacy as opposed to appropriate polypharmacy [22].

Medications which frequently lead to harm outweighing benefit in certain situations are termed “potentially inappropriate medications” (PIMs). PIMs that have been associated with ADEs have been grouped together in medication screening lists, with the most evidence-based being the STOPP criteria [23]. Randomized trials in Europe show that use of the STOPP criteria as a trigger for medication review for hospitalized seniors can improve the appropriateness of prescribing, reduce ADEs, and reduce length of stay [24, 25]. A Canadian study found that nearly 40% of seniors fill a prescription for at least one PIM per year, with the highest rates in women > 85 years of age and the most common PIM drug category being sedative-hypnotic drugs [26]. The cost of these PIMS plus the cost of treating their adverse effects was estimated to be more than US $1.8 billion annually [26].

### Priority medications

Although STOPP is an excellent screening tool, there are too many alerts (80 in current iteration) to feasibly apply in hospitalized patients where timely discharge is a high priority [25]. Analyses of Canadian and US data on drug-related causes of hospitalization by our group and others suggest recurring groups of very commonly used medications as the main causes of drug-related hospitalizations [14, 27, 28]. These are mostly medication families with proven benefit of varying clinical importance, but all cause clinically important harm when not managed well. Thus, these are medications that should trigger review of the entire medication regimen to consider improvements. We have labelled these the high-risk medications (HRM). A detailed list is shown in Appendix 1, but the main families are as follows:i.Anticoagulantsii.Analgesics including opioids, NSAIDs, and colchicineiii.Antimicrobials — long term or restrictediv.Antineoplastic agentsv.Glucose-lowering drugsvi.Cardiac drugs including diuretics and digoxinvii.Sedative-hypnotics including benzodiazepine receptor antagonists, trazodone, and baclofenviii.Antipsychotic agentsix.Other psychoactive medications including lithium, trazodone, and tricyclic antidepressantsx.Dementia medicationsxi.Immune-modulating agents such as corticosteroids

In many cases, the high-risk medication is required for the patient, but the dose may require adjustment, a tapering regimen may reduce the potential for harm, or a review for potentially serious drug interactions or medication burden identifies another medication that can be removed to decrease the patient’s overall risk of medication-related harm. We have previously developed an “Appropriateness of Prescribing Evaluation Questionnaire” that has been validated as a comprehensive medication appropriateness assessment tool [29, 30]. Optimization of high-risk medications, of course, opens up other opportunities including removal of medications and supplements with no benefit or with possibility of contamination or substitution of more cost-effective alternatives.

### Priority patients

High-cost healthcare users have been an international priority target for quality and cost of care improvements for years [31]. We have shown that 5% of 12 million citizens generate 65% of the entire healthcare costs, and approximately 70% of these are seniors with multiple hospital admissions and problematic polypharmacy [32–34]. Use of high-risk medications is very prevalent in this population and strongly predictive of future healthcare utilization and mortality in a dose- and duration-dependent manner compared to nonusers [33–36].

### Priority situations

Senior high-cost users taking high-risk medications who are transitioning into and out of hospital are at very high risk of serious ADEs. Hospitalization is a double-edged sword in that it defines high-risk situations but also houses the expertise required to effectively intervene. This opportunity to optimize medication regimens for these inpatients is widely underutilized worldwide, due to (a) huge pressures to just deal with the main problem requiring admission and get the patient discharged as quickly as possible due to bed shortages and (b) lack of expertise amongst general medicine and surgery admitting services to complete an expert medication assessment quickly. In preparation for this trial, we recently completed a chart review of 100 randomly selected senior high-cost users who were admitted to a Hamilton Hospital (mean age 82 years) and found the mean rate of potentially inappropriate medications to be 2.8 per person [37]. Only 16.6% of these had been addressed by the time of discharge [37].

## Methods

### Detailed research question

Is it feasible for an expert clinical pharmacology team to coordinate and improve medication management during the high-risk transition period from hospitalization through early post-hospital discharge follow-up for seniors who are high-cost healthcare users and taking high-risk medications, to warrant a large subsequent trial?

### Design

This is a single-center pragmatic pilot randomized trial (RCT) with 1:1 patient-level concealed-allocation randomization with blinded outcome assessment and data analysis [38]. Randomization provides the highest quality methods to minimize bias, the pragmatic design ensures relevance to clinical practice essential for implementation, and a pilot RCT addresses feasibility of a large definitive subsequent RCT directly without waste of research dollars [39, 40]. A study flow diagram is shown below in Fig. 1. Study setting is a 700-bed academic hospital with a busy urgent care and emergency department providing medical, surgical, psychiatric, and obstetric-gynecology inpatient and outpatient care in Hamilton, Ontario.

**Fig. 1 Fig1:**
[figure not shown]
IMPROVE-IT HRM flow diagram

### Participants

Adults 65 years and older who are admitted to an internal medicine acute care ward with an expected length of stay of more than 2 days, who are high-cost users defined as at least one other hospitalization within the previous year, who are taking five or more chronic medications including at least one high risk medication, and provide informed consent. Patients will be excluded if they are being discharged to long-term care or other setting where they or their caregiver is not in charge of their medications. It is estimated that at least *10 patients daily* meet these eligibility criteria.

### Recruitment and randomization

A screening tool in our EMR used by our CPT consult service for older adults taking high-risk medications provides secure messaging to our research staff. Once eligibility is confirmed, the team ensures that a best possible medication history is completed to correct the home medication list side of our discharge medication reconciliation template. Once eligibility is cleared with the most responsible physician team (primary team), research staff will then approach the patient to introduce the study and complete the informed consent process which includes completing a short Capacity to Consent questionnaire (Appendix 2) [41]. Patients with cognitive impairment will not be excluded as they constitute a vulnerable group in need of assistance, but they must have a primary caregiver who assists them with medications and who provides informed consent if the patient is identified as not having capacity of consent [41]. For this pilot trial, either the patient or caregiver must be fluent in English.

Once patients have completed baseline assessments, they will be randomly allocated to the intervention or control arms in a 1:1 ratio in permuted blocks using a statistician-formulated randomization schedule produced in R and implemented in REDCap that will be available online to staff only at the time of randomization [42, 43]. To restrict treatment group imbalance, a maximal tolerable imbalance between treatment groups will be incorporated into the schedule [44].

### Intervention

Our intervention follows the general innovative practices framework recommended by Health Quality Ontario for Transitions between Hospital and Home [45]. Fig. 2 shows a step-by-step clinical approach used for this intervention. Randomization to the intervention arm will trigger a request for a CPT (Clinical Pharmacology & Toxicology) consult. The initial CPT consult for each patient includes a comprehensive patient assessment including demographics, social situation, drug coverage insurance, functional status (activities of daily living, instrumental activities of daily living), cognition, frailty markers, level of caregiver involvement, past medical history and current problems, allergies and intolerances, detailed medication history including reminder aids and methods of accessing medication, physical exam, and review of current and historical laboratory and diagnostic imaging results. These details are mostly structured data items in the EMR which populates a customized CPT note template, which ensures some consistency of intervention across the participating consultants. We incorporate an admission medication reconciliation carried out by the ward pharmacist. The CPT consult will document a detailed “circle of care” for each patient (primary caregiver, hospital primary team, primary care team including family physician or nurse practitioner, community physician specialists and community pharmacists) and will identify all potential high-risk medications targets that the patient is taking or is due to resume post-hospitalization. Using patient preference elicitation methods and motivational interviewing, priorities for medication optimization will be negotiated [46–51]. Short patient infographics endorsed by the Canadian Medication Appropriateness and Deprescribing Network and largely addressing medication harms will be used as educational materials [52–61].

**Fig. 2 Fig2:**
[figure not shown]
IMPROVE-IT HRM clinical approach

While the patient is still hospitalized, the high-risk medications care plan begins, and the team ensures close communication with the primary team, coordinates a detailed discharge medication reconciliation (documenting medication changes with rationale, formulating an accurate discharge prescription including rapid access to new medications), ensures circle-of-care communication, and sees the patient via virtual visit twice in follow-up at 1 week and 1 month after hospital discharge to complete and consolidate the care plan. Since this is a pragmatic trial, concomitant care is not prohibited. Pre-testing of the intervention with several patients has shown that the initial consult and two follow-up visits can be completed in less than 1 h each.

### Control

These patients will receive usual care by their primary team. This means that the primary team is responsible for coordinating medication management at discharge and posthospital follow-up, as is currently practiced.

### Outcomes

The Core Outcome Set for Interventions to Improve Polypharmacy in Older People was used to inform our selection of outcomes [62]. Core outcome sets are consensus-based guidelines from groups of clinicians, patients, and methodologists on which outcomes with which metrics are the most important to be measured in prospective studies [63]. In addition, we consulted other polypharmacy/deprescribing trials for recommended patient-important outcomes [64–69].

For this pilot RCT, we will analyze outcomes according to a set of primary and secondary outcomes (see details in Tables 1 and 2).

**Table 1 Tab1:** IMPROVE-IT HRM outcomes [29, 30, 62, 64, 65, 70–73]

	**Outcome**
Feasibility	1. Participant recruitment rates
	2. Participant retention rate
	3. Trial resource utilization, costs
	4. Recommendation acceptance rates by primary team
	5. Recommendation acceptance rates by patient
	6. Recommendation adherence rates by patient
	7. CPT consultation volume capacity
	8. Potential to intervene entirely virtually (online)
Clinical	**1.** Medication management outcomes a) # inappropriate medications, # drug therapy problems improved, # high-risk medication problems improved, all measured by APEQ b) # medications per patient end study versus baseline
	**2.** Adverse drug events including adverse drug withdrawal event
	**3.** Medication errors, including preventability
	**4.** Patient problems with medications questionnaire (includes general adherence)
	**5.** Patient knowledge of medications
	**6.** Coordination and continuity of care
	**7.** Patient quality of life (EQ-5D-5L and medication-related QOL)
	**8.** Satisfaction with care (patients and providers)
	**9.** Health resource utilization, including clinical events of death, ED visits, hospitalizations, physician visits, other providers including diagnostics utilization, medication costs

**Table 2 Tab2:** IMPROVE-IT HRM study outcomes and measures

	Outcomes	Criteria for success	Outcome measure	Method of analysis	When assessed
**A. Feasibility outcomes**					
A1. Primary feasibility outcomes	A1.1 Participant recruitment rates	≥ 30% of those eligible will be considered success	Percentage recruited and rate of recruitment (of those screened, of those eligible, and of those approached)	Counts (%) over time	Baseline
	A1.2 Participant retention rate	≥ 90% is considered success	Percentage of those recruited who complete at least end-study outcome	Counts (%) end study	End of study
	A1.3 Intervention adherence	≥ 90% is considered success	Percentage of those recruited who completed each phase of the study (baseline, virtual visits, end of study outcomes)	Counts (%) over time	End of study
	A1.4 Study resource utilization	< US $1500 per patient recruited and completing the study	Study costs per patient recruited to end follow-up	Cost of personnel, supplies, travel, etc. to run the study	End of study
A2. Secondary feasibility outcomes	A2.1 Clinical Pharmacology & Toxicology (CPT) Recommendation Acceptance — Primary Team	> 50% medication recommendations	% CPT recommendations per patient accepted (continued or implemented)	Counts (%) after consult	Hospital discharge
	A2.2 CPT recommendation acceptance — patients	> 50% medication recommendations	% CPT recommendations per patient that were initially followed by patient	Counts (%) after consult	Hospital discharge
	A2.3 CPT recommendation adherence — Patients	≥ 90% is considered success	% CPT recommendations per patient still being followed at end of study	Counts (%)	End of study
	A2.4 CPT consultation volume capacity	Number of eligible patients available to approach is > 3 per day	Volume of eligible patients available to approach per week	Counts	Baseline
	A2.5 Potential to intervene entirely virtually	> 90% patients can be managed through follow-up entirely by virtual care platform	Number (%) patients entering follow-up who do not require an unscheduled in-person visit Number of follow-up visits conducted using secure videoconference platform	Counts (%)	End of study
**B. Clinical outcomes**		**Hypothesis**			
B1. Primary clinical outcomes	B1.1 Drug therapy problems improved	Intervention group will have more improved drug therapy problems compared to control group (e.g., dose adjusted, discontinued, interacting drugs removed)	Percentage of baseline drug therapy problems identified by APEQ that have been improved by end of study	Mean difference in APEQ score changes	End of study
B2. Secondary clinical outcomes	B2.1 Adverse drug events	Intervention will have lower event rates	Event rate counts from end of study interviews using Leape and Bates scale	Counts (%)	End of study
	B2.2 Medication errors	Intervention will have fever medication errors	NCC-MERP definition	Counts (%)	End of study
	B2.3 Number of medications	Intervention will have more medications deprescribed per patient	Number of medications end study compared to baseline	Counts	End of study
	B2.4 Patient problems with medications	Intervention will have fewer medication problems, including better adherence	COMPETE Medication Problems Questionnaire	Difference in mean group scores	End of study
	B2.5 Medication knowledge - patient	Intervention will have higher scores	Medication knowledge assessment form	Difference in mean group scores	Baseline and Eed of study
	B2.6 Coordination and continuity of care	Intervention will have higher ratings	Coordination and Continuity of Care Questionnaire	Difference in mean group scores	End of study
	B2.7 Patient quality of life	Intervention will improve more	EQ5D-5L and MedQOL	Difference in mean group change scores	End of study
	B2.8 Patient satisfaction with care	Intervention will have higher scores	Patient Satisfaction Questionnaire	Descriptive analysis	End of study
	B2.9 Provider satisfaction with care	Intervention will have higher scores	Physician, pharmacist Study Satisfaction Questionnaire	Descriptive analysis	End of study
	B2.10 Cost-effectiveness/ health resource utilization	Intervention will be cost-effective using a threshold of US $50,000 per QALY	Cost per adverse drug events avoided and incremental cost per quality-adjusted life-years (QALYs) using EQ5D-5L utilities	Economic analysis	End of study

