### Sample size

Since this is a pilot RCT, we will aim for 30 patients per group or 60 in total as this number is likely to provide adequate evidence regarding feasibility for ramp-up to a definitive trial.

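### Table 2, A1.3: the ≥ 90% intervention-adherence criterion is set on all recruited patients, although only the intervention arm is scheduled for the virtual visits it counts

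*Protocol article*

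**What the plan says.** Table 2 of the protocol article lists "A1.3 Intervention adherence" under primary feasibility outcomes. Its measure is "Percentage of those recruited who completed each phase of the study (baseline, virtual visits, end of study outcomes"), its criterion is "≥ 90% is considered success", and its method of analysis is counts and percentages over time. The line above it, A1.2 (retention), uses the same base for the whole trial: "Percentage of those recruited who complete at least end-study outcome".

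Under Recruitment and randomization, consented patients who have completed baseline assessments are "randomly allocated to the intervention or control arms in a 1:1 ratio". Under Sample size, "we will aim for 30 patients per group or 60 in total".

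The virtual visits are described under Intervention, where the team "sees the patient via virtual visit twice in follow-up at 1 week and 1 month after hospital discharge". Under Control, "These patients will receive usual care by their primary team", and that team is also responsible for follow-up after discharge. Table 3 marks the clinical pharmacology consult at 1 week and 1 month for the intervention group only, and no row of that table has a control entry at either time.

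**The concern.** The name of the outcome, its base and one of its components do not fit together. The name points to the intervention arm. The base, patients recruited, is both arms, because recruitment precedes randomization and A1.2 uses the same words for the whole trial. One of the three listed phases, the virtual visits, is scheduled in one arm only.

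A1.3 is the only line in Table 2 that measures whether the scheduled virtual visits were completed. A2.5 concerns unscheduled in-person visits and the platform used, which is a different question. The research question asks whether the team can feasibly deliver this management through early follow-up after discharge. If the one criterion aimed at delivery of the visits is set on the wrong base, its result will not answer that part of the question, whichever way the base is read.

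**Working it through.** **Inputs.** Planned size N = 60, with 30 per arm (Sample size). Threshold 90% of those recruited (Table 2, A1.3). Virtual visits scheduled in the intervention arm only (Intervention, Control, Table 3). The protocol derives neither the sample size nor the 90% by formula, so there is no calculated figure to reproduce beyond 30 + 30 = 60, which agrees.

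**Step 1: the criterion as written.** 90% of 60 is 0.90 × 60 = 54 patients. At most the 30 intervention patients can complete the virtual-visit phase, so its maximum is 30/60 = 50%. A chance imbalance in arm sizes hardly moves this: 32/60 = 53%. Reporting one percentage per phase does not help, because the virtual-visit percentage over all recruited has the same ceiling.

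**Step 2: controls credited for baseline and end of study only, one pooled percentage.** Intervention completers needed = 54 − control completers.

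| Controls completing (of 30) | Intervention completers needed (of 30) |
|---|---|
| 30 | 24 (80%) |
| 29 | 25 (83%) |
| 28 | 26 (87%) |
| 27 | 27 (90%) |
| 26 | 28 (93%) |

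The pooled mark is looser than 90% in the intervention arm if more than 27 controls complete, and stricter if fewer do.

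**Step 3: chance of passing.** Let X be the number of completers in the intervention arm and Y the number in the control arm, independent binomials with 30 patients each. The pooled rule passes with probability P(X + Y ≥ 54), and a rule on the intervention arm alone with P(X ≥ 27). The protocol gives no expected completion rates, so the rates below are assumptions shown as a range.

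| True completion, intervention | ≥ 27/30, intervention arm only | Pooled, controls 85% | 90% | 95% | 97% | 100% |
|---|---|---|---|---|---|---|
| 80% | 0.12 | 0.08 | 0.18 | 0.36 | 0.45 | 0.61 |
| 85% | 0.32 | 0.18 | 0.36 | 0.61 | 0.71 | 0.85 |
| 90% | 0.65 | 0.36 | 0.61 | 0.84 | 0.91 | 0.97 |

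At a given intervention completion, the chance of passing the pooled rule depends heavily on what the controls do: with 80% in the intervention arm it runs from 0.08 to 0.61.

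**The case against.** The strongest defence is that the intent is plain. The outcome is called intervention adherence, the visits are described under Intervention, and Table 3 schedules them for that group alone. No sensible analyst would score controls as failing visits they were never offered, so the 50% ceiling comes from loose wording in a condensed table cell. The probable intent stands. It does not remove the defect, because the measure column states a base and nothing in the article restricts A1.3 to one arm or says how controls count.

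A second defence is that counts over time may mean a percentage for each phase, so that controls could not mask poor visit completion. That is a fair reading, and it limits Steps 2 and 3 to the pooled one. The virtual-visit phase would still need a base, and the stated one caps it at 50%.

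A third is that the Follow-up section has follow-up visits by videoconference or telephone without naming an arm. In Table 3, however, the only control assessment after discharge is at 3 months, and A1.3 lists end-of-study outcomes as a separate phase. That visit cannot supply the virtual visits for controls.

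Two stronger readings are tempting, and the document does not support them. A reader might infer that a primary go/no-go rule is bound to fail. Table 1, the Primary outcomes section and the Statistical analyses section do not name A1.3; the last two name recruitment, retention and resources. The feasibility analysis is to be descriptive, and no section makes A1.3 a condition for the definitive trial. A reader might also infer that controls necessarily inflate the result. That needs the pooled reading and high control completion. At 90% control completion, the retention target, the pooled rule passes 0.18 against 0.12 (intervention 80%) or 0.36 against 0.32 (85%). At 85% control completion it is the stricter of the two. Follow-up ends at death or admission to long-term care, so very high completion cannot be taken for granted in this population.

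**Conclusion.** A1.3 is a mis-specified feasibility criterion. With 1:1 allocation and 30 patients per arm, the virtual-visit phase on the stated base cannot exceed about 50% against a threshold of 90%. This follows from the protocol's own figures and needs no outside assumption. Under the alternative of one pooled percentage with controls credited, the pass mark in the intervention arm shifts with control completion, from 24 of 30 (all controls complete) to 28 of 30 (26 complete). The direction and size of that shift rest on assumed completion rates.

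The reach is limited. Randomization, data collection, the clinical outcomes and the three feasibility outcomes named in the text are not affected. What is lost is a usable reading of whether the scheduled virtual visits were delivered.

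**What to change.** In the A1.3 line of Table 2, replace those recruited with those randomized to the intervention arm, and apply the 90% threshold (0.90 × 30 = 27 of 30) to completion of the scheduled virtual visits on that base. End-of-study completion in both arms needs no further provision, since A1.2 already covers it with its own 90% threshold.

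When that line is edited, state whether A1.3 is a primary feasibility outcome, so that Table 2 agrees with Table 1 and with the Primary outcomes and Statistical analyses sections.

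The cost is one line of text, with no new data and no change to care or visits.
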